### Go Nisha Go mobile game

Go Nisha Go™ (GNG) is a role-play, simulation game [8], mobile app that follows the life of a young Delhi-based protagonist, Nisha, as she embarks on a journey of self-discovery and agency. Played across five levels, the game uses an aspirational [9] travel theme that has Nisha visiting the Indian cities of Sikkim, Mumbai, Goa, and Hyderabad, while meeting inspirational women (a scientist, an influencer, a nurse, and a police officer), as part of her internship for a web series production. Hindi is the spoken language of the game and Hinglish (Hindi language written in Latin script) is the script of the game. Thus, the interaction and communication with the game is made effortless [6]. Each level focuses on specific game-based objectives related to menstrual health, fertility awareness, contraception, and consent, scaffolded on outcomes related to negotiation, relationship obligation, health knowledge, and confidence. The game is designed to increase knowledge incrementally (and subsequently the confidence and efficacy to make better choices) through strategically placed ‘nudges’ in the gameplay, trade-offs/rewards, minigames, and direct access to resources such as educational videos and a chatbot. The game does not collect any Personally Identifiable Data (PID), thus protecting players’ privacy.

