#### Outcomes measures

The baseline and follow-up survey tools are created with the previously tested tools from standard studies such as the UDAYA study (Understanding the lives of adolescents and young adults) [3], National Family Health Survey (NFHS) [18], Comprehensive National Nutrition Survey (CNNS) [19], Living Standards Measurement Study [20], and other national surveys in India [21]. The primary outcome of the evaluation is to measure improvement in the existing knowledge of MHM, contraception, and increased in agency for adolescent girls making informed decisions and choices in their lives (See Table 4). Several other secondary outcomes measuring intended behaviour change and agency with respect to improvement in decision making, choice of career, negotiation in relationships, and assertion of self-identity will also be evaluated.

**Table 4 Tab4:** List of selected outcome indicators for the study

Outcome indicators	Contents of measurement
Menstrual health management	Percentage of girls who have: - Received any information about MHM - Awareness about sanitary napkins - Awareness about different menstrual hygiene products - Obtained menstrual products alone - Practiced tracking their menstruation with comprehensive understanding of fertility awareness - Experienced trouble in obtaining menstrual hygiene products - Bought menstrual hygiene products online
Contraception	Percentage of girls who have: - Awareness about modern contraceptive methods - Comprehensive knowledge about Oral contraception pills - Comprehensive knowledge about Emergency contraception pills - Comprehensive knowledge about condoms - Comprehensive knowledge about IUD - Comprehensive knowledge about injectables - Practiced refusing sex due to non-availability of contraception - Awareness about condom’s use for prevention of pregnancy and/or infections

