#### Data analysis plan

Analyses will test whether participants who played the game (treatment arm) relative to control participants who have not received any encouragement to play the game:Improved knowledge about SRH care, including menstruation, menstrual hygiene, fertility awareness, and SRH/menstrual management products.Improved attitudes, confidence, and decision support for managing her self-care, SRH, negotiating consent and contraceptive use, and accessing/using DTC information, products, and care.Improved assertion of self-identity through DTC linkages to career, safety, and personal well-being resources, and improved self-efficacy.

Analysis of the quantitative study data will be conducted using STATA and SPSS where appropriate. Descriptive analysis will be performed for all variables, and unadjusted comparisons between experimental and control arms will be conducted. Descriptive statistics will be performed, including frequencies, means, and standard deviations. In addition, chi-square tests and t-tests will be used to examine associations in the data. A probability value of less than 0.05 will be considered statistically significant for all statistical tests conducted. Continuous variables will be tested for normality, and non-normal values will be categorised or transformed appropriately.

The following two analyses will be done to satisfy the objective of the study:Univariate descriptive analysis such as frequency, percentages, the mean, and standard deviation will be computed for different background characteristics and knowledge, attitude, and practice (KAP) variables.KAP variables will be analyzed using Z-test/t-test for encouragement and control arms in two points from the same respondent.The net change in KAP and its significance will be calculated using difference-in-difference (DID) analysis. The DID analysis will be done using the following formula. (See Table 5)

**Table 5 Tab5:** Difference-in-difference analysis pathway in RCT

	Experimental arm (s = 2)	Control arm (s = 1)	Difference (s)
Baseline (t = 1)	Y_12_	Y_11_	Y_21_ –Y_11_
Follow-up (t = 2)	Y_22_	Y_21_	Y_22_ –Y_12_
Difference (t)	Y_22_ –Y_21_	Y_12_ –Y_11_	Net change (DID) = (Y_22_ – Y_21_) – Y_12_ – Y_11_

The level of significance of DID will be tested using the below equation through regression analysis.$${\text{Y }} = {\text{ a }} + {\text{ b}}_{{{\text{1s}}}} + {\text{ b}}_{{{\text{2t}}}} + {\text{ b}}_{{{\text{3s}}*}}$$

where.

Y = dependent/response variable.

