a = constant.

s and t are study arm and time, respectively.

b_1_ and b_2_ are slopes for the study arm and time, respectively.

b_3_ = treatment effect.

s*t is a dummy variable indicating treatment status.

The significance level of the test will be measured using a p-value < 0.05 (95% level of significance as per the sample size estimation).

The primary comparison of the binary outcomes between intervention groups at baseline and follow-up will use mixed-effects longitudinal logistic regression, with random effects for the individual over time. The baseline will be included as a time point only. A categorical time effect will be used (profile model). A “difference-in-differences” analysis will compare the treatment arms. Statistically, this amounts to testing for an interaction between time and treatment arm in the longitudinal model. Since the treatment assignment is at random, this “unadjusted” analysis will provide a causal effect of the intervention. However, we will also conduct secondary analyses, adjusting for potentially relevant covariates (e.g., age, education, etc.), in addition to time and treatment arm, using backward model selection at the α = 0.15 threshold level. These secondary analyses may improve the precision (power) of estimating the treatment effect and reduce any bias due to random imbalances between arms.

The primary analyses will use an intent-to-treat approach and analyze all subjects according to a randomized group. For subjects missing the follow-up survey, we will impute data from the lower (worse) half of the distribution by the arm (conservative approach). We will also conduct dose analyses, in which we include only those subjects who complete the full intervention. Analyses will use data only for outcomes; (a) increased comprehensive contraceptive knowledge, (b) MHM (c) negotiation and self-efficacy. We will conduct exploratory analyses using outcomes.

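### Knowledge of each contraceptive method is scored only as a yes/no comprehensive indicator, so smaller gains do not register: add a graded score beside it and drop the rule that categorises non-normal variables

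*Protocol article*

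**What the plan says.** Outcomes measures states the aim: "The primary outcome of the evaluation is to measure improvement in the existing knowledge of MHM, contraception", together with agency. The section on the game describes the mechanism: "The game is designed to increase knowledge incrementally".

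Every entry in the contraception row of Table 4 is a percentage of girls. Knowledge of the five individual methods appears as a comprehensive-knowledge percentage for each, such as "Comprehensive knowledge about Oral contraception pills". The same row has two knowledge entries with a lower bar: "Awareness about modern contraceptive methods", and awareness of the condom's "use for prevention of pregnancy and/or infections". The table is titled "List of selected outcome indicators for the study", so it does not claim to be complete.

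The Data analysis plan then fixes the scale: "The primary comparison of the binary outcomes between intervention groups at baseline and follow-up will use mixed-effects longitudinal logistic regression". It names comprehensive contraceptive knowledge among the outcomes to be analysed. For continuous variables it prescribes a normality test, after which "non-normal values will be categorised or transformed appropriately". The article names no graded knowledge score.

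**The concern.** An indicator of comprehensive knowledge has two values. A girl who knows more about a method at follow-up than at baseline, but is on the same side of the cut-off both times, contributes no change. If the game moves many girls part of the way, the indicator sees only those who happen to cross. The trial could then report little or no effect on a primary outcome while knowledge had in fact improved.

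The normality rule would compound this. A count of correct answers is bounded and discrete, so with 1,950 girls a normality test would almost surely reject it. The rule would then permit the count to be cut into categories again.

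**Working it through.** **Inputs from the article.** 1,950 girls, 650 per site (3 × 650 = 1,950), allocated 975 per arm (1,950 / 2 = 3 × 325 = 975); significance level 0.05. The article gives no effect size, prevalence, standard deviation or power beside the sample size, so there is no stated power figure to reproduce.

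**Assumptions.** Two-sided tests, a comparison at follow-up only, no dropout. The prevalence of comprehensive knowledge, the number of items and the cut-off are unknown and are varied.

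**Step 1: information kept by a yes/no cut of a normal score.** If a share *p* of girls passes the threshold and *z* = Φ⁻¹(1 − *p*), the efficiency relative to the uncut score is φ(*z*)² / [*p*(1 − *p*)].

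- *p* = 0.50: 0.3989² / 0.25 = 0.637
- *p* = 0.05: 0.1031² / 0.0475 = 0.224

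**Step 2: what this means with 975 per arm.** The shift that a graded score detects with 80% power is (1.960 + 0.842) × √(2/975) = 0.127 SD. The same shift, seen through a threshold:

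| Controls above threshold | Treated above threshold | Information kept | Power, yes/no | n per arm for 80% power |
|---|---|---|---|---|
| 50% | 55.1% | 0.64 | 61% | 1,532 |
| 30% | 34.6% | 0.58 | 58% | 1,654 |
| 20% | 23.7% | 0.49 | 52% | 1,915 |
| 10% | 12.4% | 0.34 | 39% | 2,681 |
| 5% | 6.5% | 0.22 | 28% | 4,016 |
| Graded score | – | 1 | 80% | 974 |

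**Step 3: discrete item scores and different cut-offs.** Take 4 or 5 items per girl, a logit mean from −1.5 to 0, a between-girl SD of 1 on the logit scale and a shift of 0.18.

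- 5 items, all required: power 13% to 36% for the indicator, 74% to 81% for the number correct.
- 4 items, all required: 16% to 42% against 67% to 77%.
- Softer cut-offs at logit mean 0: at least 4 of 5 gives 61% and at least 3 of 5 about 66%, against 81% for the score; at least 3 of 4 gives 61% against 76%.

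Across these cut-offs the indicator has about 13% to 66% power and the score about 67% to 81%.

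**Step 4: a different item model.** Each item's correct rate rises by 5 percentage points from 40–60%, and all items must be correct. With 3 to 5 items and a within-girl correlation of 0.3 to 0.5, power is 52% to 79% for the indicator and 77% to 93% for the score. With 3 to 6 independent items it is 22% to 85% against 97% or more.

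In every setting the indicator has less power than the score. The size of the gap varies widely.

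**Step 5: the normality rule.** With about 975 girls per arm, the difference in mean score is close to normally distributed even when the score is not, and robust standard errors allow for unequal variances. Categorising therefore solves no problem here, and it discards information as in Step 1.

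**The case against.** Several points on the other side are sound.

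- **Comprehensive knowledge is a declared target.** It is in the study objective (Evaluation framework and theory of change) and again in the Data analysis plan. How many more girls are well informed is a fair question, and a mean score answers a different one. A reader might infer that the percentage is the wrong endpoint and should be replaced. The documents do not support that.
- **The contraception row is not limited to comprehensive knowledge.** The two awareness items can pick up some smaller gains. Both are still yes/no, and neither measures graded knowledge of pills, emergency pills, IUD or injectables.
- **The cut-off is not defined in the article.** One might conclude that a girl who goes from no facts to most of them counts as unchanged. That holds only if the cut-off lies above most, which cannot be known here. Leaving the definition to the full protocol or questionnaire is normal for an article and is not itself a fault. For the same reason the lowest power figures, which require every fact to be correct, cannot be taken as the trial's power.
- **Incremental learning may describe delivery.** The phrase can refer to how content is built up through play, and need not predict a partial effect at follow-up. The stated primary outcome, improvement in existing knowledge, carries the point without it.
- **A score is not ruled out.** Table 4 is a selection, and means and t-tests are planned for knowledge, attitude and practice variables. That leaves room for a score but does not commit to one, and the primary comparison is explicitly binary.
- **The normality rule does not touch indicators that are already binary**, and it offers transformation as an alternative. It would matter only once a score exists, which is the reason to correct it when one is added.

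**Conclusion.** The point holds for the five method-specific indicators: they register only threshold crossings, they feed a binary primary comparison, and no graded measure is specified beside them, although the stated aim is improvement in knowledge. The direction of the loss is the same in every setting computed. Its size is conditional: 36% to 78% of the information under a normal score with 50% down to 5% of girls passing, and power of about 13% to 66% against 67% to 81% in the simulations of Step 3, with milder gaps under some of the Step 4 assumptions. These are ranges under assumed prevalences, item counts and cut-offs, not estimates for this trial.

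A reader might also infer that the answers needed for a score are already collected. Table 3 shows a section on knowledge of contraceptive methods, but not that each method has several scored items, so the remedy has to be conditional on that.

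**What to change.** 1. Keep the percentage with comprehensive knowledge for each method.
2. Where the questionnaire has several items per method, prespecify as a key supporting analysis the number or proportion of contraceptive-knowledge items answered correctly, compared between arms by a linear model with robust standard errors.
3. In the Data analysis plan, remove categorisation from the rule for non-normal continuous variables and analyse them on their original scale.

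The cost is one more analysis per knowledge domain, and a mean score that is less easy to communicate than a percentage, which is why the percentage stays. If the survey holds several items per method, no new data are needed. If it does not, only item 3 can be adopted without changing the survey tool.

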#### Data analysis plan

Analyses will test whether participants who played the game (treatment arm) relative to control participants who have not received any encouragement to play the game:Improved knowledge about SRH care, including menstruation, menstrual hygiene, fertility awareness, and SRH/menstrual management products.Improved attitudes, confidence, and decision support for managing her self-care, SRH, negotiating consent and contraceptive use, and accessing/using DTC information, products, and care.Improved assertion of self-identity through DTC linkages to career, safety, and personal well-being resources, and improved self-efficacy.

Analysis of the quantitative study data will be conducted using STATA and SPSS where appropriate. Descriptive analysis will be performed for all variables, and unadjusted comparisons between experimental and control arms will be conducted. Descriptive statistics will be performed, including frequencies, means, and standard deviations. In addition, chi-square tests and t-tests will be used to examine associations in the data. A probability value of less than 0.05 will be considered statistically significant for all statistical tests conducted. Continuous variables will be tested for normality, and non-normal values will be categorised or transformed appropriately.

The following two analyses will be done to satisfy the objective of the study:Univariate descriptive analysis such as frequency, percentages, the mean, and standard deviation will be computed for different background characteristics and knowledge, attitude, and practice (KAP) variables.KAP variables will be analyzed using Z-test/t-test for encouragement and control arms in two points from the same respondent.The net change in KAP and its significance will be calculated using difference-in-difference (DID) analysis. The DID analysis will be done using the following formula. (See Table 5)

**Table 5 Tab5:** Difference-in-difference analysis pathway in RCT

	Experimental arm (s = 2)	Control arm (s = 1)	Difference (s)
Baseline (t = 1)	Y_12_	Y_11_	Y_21_ –Y_11_
Follow-up (t = 2)	Y_22_	Y_21_	Y_22_ –Y_12_
Difference (t)	Y_22_ –Y_21_	Y_12_ –Y_11_	Net change (DID) = (Y_22_ – Y_21_) – Y_12_ – Y_11_

The level of significance of DID will be tested using the below equation through regression analysis.$${\text{Y }} = {\text{ a }} + {\text{ b}}_{{{\text{1s}}}} + {\text{ b}}_{{{\text{2t}}}} + {\text{ b}}_{{{\text{3s}}*}}$$

where.

Y = dependent/response variable.

a = constant.

s and t are study arm and time, respectively.

b_1_ and b_2_ are slopes for the study arm and time, respectively.

b_3_ = treatment effect.

s*t is a dummy variable indicating treatment status.

The significance level of the test will be measured using a p-value < 0.05 (95% level of significance as per the sample size estimation).

The primary comparison of the binary outcomes between intervention groups at baseline and follow-up will use mixed-effects longitudinal logistic regression, with random effects for the individual over time. The baseline will be included as a time point only. A categorical time effect will be used (profile model). A “difference-in-differences” analysis will compare the treatment arms. Statistically, this amounts to testing for an interaction between time and treatment arm in the longitudinal model. Since the treatment assignment is at random, this “unadjusted” analysis will provide a causal effect of the intervention. However, we will also conduct secondary analyses, adjusting for potentially relevant covariates (e.g., age, education, etc.), in addition to time and treatment arm, using backward model selection at the α = 0.15 threshold level. These secondary analyses may improve the precision (power) of estimating the treatment effect and reduce any bias due to random imbalances between arms.

The primary analyses will use an intent-to-treat approach and analyze all subjects according to a randomized group. For subjects missing the follow-up survey, we will impute data from the lower (worse) half of the distribution by the arm (conservative approach). We will also conduct dose analyses, in which we include only those subjects who complete the full intervention. Analyses will use data only for outcomes; (a) increased comprehensive contraceptive knowledge, (b) MHM (c) negotiation and self-efficacy. We will conduct exploratory analyses using outcomes.

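### The primary outcome spans three domains and 24 binary indicators with no lead endpoint, every test is fixed at an unadjusted p<0.05, and agency sits in both the primary and the secondary tier

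*Protocol article*

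**What the plan says.** **Primary outcome.** Under Outcomes measures: "The primary outcome of the evaluation is to measure improvement in the existing knowledge of MHM, contraception, and increased in agency". The sentence refers to Table 4.

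**Table 4.** It lists indicators as percentages of girls: 7 for MHM, 8 for contraception and 9 for agency. The MHM row begins "Received any information about MHM - Awareness about sanitary napkins - Awareness about different menstrual hygiene products". No indicator is marked as leading, and no score, ordering or success rule is given.

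**Secondary outcomes.** The next sentence reads: "Several other secondary outcomes measuring intended behaviour change and agency with respect to improvement in decision making". It goes on to name negotiation in relationships, choice of career and self-identity. Table 4 labels its agency row with decision making, negotiation and consent.

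**Threshold.** The Data analysis plan says "A probability value of less than 0.05 will be considered statistically significant for all statistical tests conducted". For the difference-in-difference test it repeats: "The significance level of the test will be measured using a p-value < 0.05".

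**Model and outcome list.** The primary comparison is a mixed-effects logistic regression of the binary outcomes, with the time-by-arm interaction as the effect. Near its end the section says: "Analyses will use data only for outcomes; (a) increased comprehensive contraceptive knowledge, (b) MHM (c) negotiation and self-efficacy".

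**The concern.** A single primary outcome that is really three domains and 24 indicators gives many routes to a significant result. The plan does not say which route counts, and it sets the same uncorrected threshold for each. The primary model is for binary outcomes in the plural, so nothing in the text collapses a domain into one test.

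The tiers are also unsettled. Decision making and negotiation are primary in one sentence and secondary in the next, and the Data analysis plan names the third domain in other words (negotiation and self-efficacy). An agency result could be reported in either tier.

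At stake is whether a positive finding can be read as confirmatory. The Discussion says that the study is expected to show gains and hopes that it will support wider uptake of the game.

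**Working it through.** **Is there a figure to reproduce?** No. The article states a per-test level of 0.05 but no family-wise error rate. It gives no power, effect size or base rates.

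**Inputs from the document**
- Indicators (Table 4): 7 + 8 + 9 = 24.
- Level per test: 0.05, unadjusted (Data analysis plan).

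**Assumptions, because the document is silent**
- Tests are two-sided, so 0.025 falls in the favourable direction.
- There is no true effect on any indicator.
- Any one significant indicator could be presented as success.
- Correlation between test statistics is unknown and is varied below.

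**Step 1: 24 independent tests**
- Either direction: 1 − 0.95^24 = 0.708. Expected false positives: 24 × 0.05 = 1.2.
- Favourable direction only: 1 − 0.975^24 = 0.455. Expected: 24 × 0.025 = 0.6.

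The expected counts do not depend on correlation.

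**Step 2: correlated tests.** Simulated normal test statistics in blocks of 7, 8 and 9, with the between-domain correlation set at half the within-domain value:

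| Within-domain correlation | Either direction | Favourable only |
|---|---|---|
| 0 | 0.708 | 0.455 |
| 0.2 | 0.675 | 0.385 |
| 0.4 | 0.597 | 0.320 |

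With one common correlation of 0.5 across all 24, the figures are 0.458 and 0.230. Against the nominal 0.025, the favourable column is 0.320/0.025 ≈ 13 to 0.455/0.025 ≈ 18 times too high.

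**Step 3: one unadjusted test per domain, independent**
- Either direction: 1 − 0.95^3 = 0.143.
- Favourable only: 1 − 0.975^3 = 0.073.

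**Step 4: sidedness.** If each test were one-sided at 0.05, the favourable figures would be 0.708 if independent, and about 0.60 and 0.50 at within-domain correlations of 0.2 and 0.4.

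**Step 5: price of a correction over three endpoints.** The strictest Holm step is 0.05/3 = 0.0167, with critical value 2.394. At an assumed 80% power, the ratio of detectable effects is (2.394 + 0.842)/(1.960 + 0.842) = 3.236/2.802 = 1.155.

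**The case against.** **Multiplicity is usually settled in the analysis plan.** Silence could be left there. This article is not silent: it fixes 0.05 for every test and again for the treatment effect, so an analysis plan that adjusted would contradict it. The double placement of agency is likewise on the page. This objection does not stand.

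**The document does not say that any one indicator counts as success.** This is correct. Table 4 is headed as a list of selected indicators, and the primary outcome is stated at domain level. The 24-test figures describe what the plan permits, not a rule it states. That is why the three-test figures are given as well.

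**The error rate may be overstated.** A reader might infer from 71% that a false claim that the game works is more likely than not. The document does not support that. The 71% counts errors in both directions and needs independence. A false claim of benefit needs an error in the favourable direction, which at two-sided 0.05 is at most 46%, and less with correlation. It would pass one half only with one-sided tests at 0.05 and low correlation, and sidedness is not stated.

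**The overlap is partial and the third wording may be drift.** Both are fair. Choice of career and self-identity are not named in Table 4's agency row, so the overlap is confined to decision making and negotiation. The list in the Data analysis plan is recognisably the same three domains, and because it follows the sentence on dose analyses, its scope is unclear. It should be aligned, but it is not a competing outcome set.

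**Conclusion.** The point holds. The plan names no lead endpoint among 24 indicators in three primary domains, fixes an unadjusted 0.05 for all tests, and places part of agency in two tiers.

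The excess error is large on any any-item reading. It depends on two things the document leaves open, the success rule and sidedness, and on an unknown correlation. Even the mildest reading, one test per domain, nearly triples the nominal rate.

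This needs correcting before a positive result can be treated as confirmatory.

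**What to change.** 1. Name one primary endpoint per domain. This can be a single Table 4 indicator, analysed with the logistic model already planned. Alternatively it can be a domain score, with a stated denominator for items that do not apply to every girl (for example, those on attending college or on refusing sex) and a model suited to a score.
2. Test the three endpoints with Holm at a family-wise 0.05, and state the sidedness and what counts as success.
3. Label all other indicators secondary, with false-discovery-rate control or without confirmatory claims.
4. Replace the sentence that applies p<0.05 to all tests, and the matching sentence for the difference-in-difference test.
5. Place agency in one tier, and use the same words for it in Outcomes measures and in the Data analysis plan.

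**Cost.** With single indicators this is a change of wording and needs no new data. A domain score also requires a new primary model, because the stated one is for binary outcomes. At the strictest Holm step the detectable effect is about 15% larger, assuming 80% power, which the document does not state.

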**Methods:**

A two-arm RCT will be conducted in three cities in India: Patna, Jaipur, and Delhi-NCR. The first arm is the treatment (encouragement) arm (n = 975) where the participants will be encouraged to download and play the game, and the second arm (n = 975) where the participants will not receive any nudges/encouragement to play the game. They may or may not have access to the game. After the baseline recruitment, participants will be randomly assigned to these two arms across the three locations. Participants of the treatment/encouragement arm will receive continuous support as part of the encouragement design to adopt, install the game from the Google Play Store at no cost, and play all levels on their Android devices. The encouragement activity will continue for ten weeks, during which participants will receive creative messages via weekly phone calls and WhatsApp messages. We will conduct the follow-up survey with all the participants (n = 1950) from the baseline survey after ten weeks of exposure. We will conduct 60 in-depth qualitative interviews (20 at each location) with a sub-sample of the participants from the encouragement arm to augment the quantitative surveys.

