### RCT study

#### Sample size

The study proposes recruiting 1,950 participants from three sites: 650 girls each from Patna, Jaipur, and Delhi NCR for in-person interviews. In addition, 60 girls (n = 20 each from Patna, Jaipur, and Delhi NCR) will be recruited purposively from the encouragement arm of 975 participants for qualitative in-depth interviews. During the encouragement design activity, half of the participants (i.e., 325 girls each from Patna, Jaipur, and Delhi NCR) will receive nudges/encouragement to play the game.

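### A normality test decides whether continuous variables are categorised or transformed, but it does not show whether the comparison of means is valid (minor, cheap to fix)

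*Protocol article*

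**What the plan says.** The rule stands in the Data analysis plan of the protocol article: "Continuous variables will be tested for normality, and non-normal values will be categorised or transformed appropriately". It names no test, threshold, cut point or transformation.

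The same section describes the analyses that continuous variables would enter. Means and standard deviations are computed for background characteristics and for knowledge, attitude and practice (KAP) variables. In general, "chi-square tests and t-tests will be used to examine associations in the data". For KAP, "KAP variables will be analyzed using Z-test/t-test for encouragement and control arms in two points from the same respondent". Net change is then estimated by a difference-in-differences regression. Age is given as an example covariate for the secondary adjusted models.

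On size, "The study proposes recruiting 1,950 participants from three sites", and the Sample size section puts 975 of them in the encouragement arm. On the error rate: "A probability value of less than 0.05 will be considered statistically significant for all statistical tests conducted".

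Two statements limit the rule's reach. Every indicator in Table 4 is a percentage of girls, and the primary comparison is a mixed-effects logistic regression of binary outcomes.

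**The concern.** A normality test asks whether the raw values follow an exact Gaussian distribution. What the analysis needs to know is whether the difference in means between arms, and its standard error, can be trusted. In a small sample the two questions overlap. With 975 per arm they largely separate: the arm mean is close to normally distributed even when single values are discrete, bounded or skewed, while a normality test on 1,950 values has enough power to detect harmless departures.

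A variable could therefore be taken off its own scale when nothing was wrong with the planned comparison. If it is categorised, information already collected is discarded. If it is transformed, the effect is estimated on another scale. For a covariate such as age, categorising works against the gain in precision that the adjusted models are meant to bring.

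**Working it through.** **Inputs from the protocol.** 1,950 girls, 975 per arm; significance level 0.05, taken here as two-sided because sidedness is not stated. The article refers to a sample size calculation ("95% level of significance as per the sample size estimation") but shows no power, effect size or standard deviation, so there is no figure to reproduce. No dropout rate is given, so the full 975 per arm are used.

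**Assumption.** 80% power for the uncut score. The detectable difference is then (1.960 + 0.842) × √(2/975) = 2.802 × 0.0453 = 0.127 SD.

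**Step 1. Does the t-test need Gaussian values here?** In 20,000 simulated two-arm comparisons per distribution (975 per arm), type I error was 4.75% to 5.2% throughout. The distributions were integer scores of 0–10, 0–20 and 0–30, whole-year age 15–19, gamma, t with 10 degrees of freedom, and lognormal.

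**Step 2. What would the trigger do at n = 1,950?** Share of simulated samples in which normality was rejected:

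| Variable (assumed) | Shapiro-Wilk | D'Agostino |
|---|---|---|
| Symmetric binomial score 0–10 | 100% | 37% |
| Symmetric binomial score 0–30 | 100% | 5.5% |
| Beta-binomial scores 0–10 and 0–20 | 100% | 100% |
| Age 15–19 in whole years | 100% | 100% |
| Continuous, skewness 0.28 | 99.5% | 99.5% |
| Continuous, skewness 0.14 | 58% | 61% |
| Exactly normal | 6% | 4.5% |

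The result depends on the variable and on which test is used. In none of these rows did the t-test lose its level.

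**Step 3. What would categorising cost?** For a normal score cut at quantile q, with c the matching normal quantile, the relative efficiency is φ(c)² / [q(1 − q)]. Power after the cut is Φ(2.802 × √efficiency − 1.960).

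- Median: efficiency 2/π = 0.637; Φ(2.236 − 1.960) = 60.8%. This is the information of about 0.637 × 1,950 ≈ 1,240 girls.
- 70th percentile: 0.576; 56.6%.
- 80th percentile: 0.490; 50.0%.
- 90th percentile: 0.342; 37.4%.
- Equal ordered groups scored by their means: tertiles 0.793, 70.4%; quartiles 0.861, 73.9%; quintiles 0.897, 75.6%.

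Starting from 90% or 95% power, a median split gives 73.4% or 82.0%. Simulated integer scores cut near the median fell from about 79–81% to 61–66%, which agrees with the formula. For a lognormal variable shifted by the same 0.127 SD, a median split raised power from 79% to 99.5%. No loss was computed for transformation.

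**The case against.** The strongest reply is that the rule may touch nothing important. All Table 4 indicators are percentages, the primary model is logistic, and the article names no summed score or rating scale as an outcome. Planning a Z-test or t-test for KAP variables does not prove that such scores exist, since a Z-test suits percentages. The only named variable in the calculations is age, which is a covariate, and the power figures for cutting an outcome do not apply to it. All of this stands, and it sets the severity.

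Three stronger readings are tempting and are not supported.

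- A reader might infer that usable scores lose up to about 20 points of power. That is one assumed case, a median split of a roughly normal score with about 80% power. It is not a ceiling (an 80th-percentile cut loses 30 points) and not typical (quintiles lose about 4). The rule also allows transformation, for which no loss is shown.
- A reader might infer that every survey variable would be rejected. This holds for Shapiro-Wilk on integer scores but not for every test, and the article names none.
- A reader might infer a raised false-positive rate from cut points chosen after the data are seen. The article does not say that cuts will be chosen that way, and cut points are commonly left to a fuller protocol or analysis plan that is not shown.

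What the reply does not rescue is the trigger itself. It is a stated rule, not a detail left for later.

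**Conclusion.** The point holds as a minor one. The plan makes recoding of continuous variables depend on a test that does not track whether the comparison of means is valid: with 975 per arm the t-test kept its level in every distribution tried, whatever the normality test said.

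The primary comparison and the Table 4 indicators are unaffected. The rule reaches only KAP variables analysed by means and t-tests, if there are any, and continuous covariates.

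The size is conditional on figures the article does not give. From an assumed 80% power for a roughly normal score, categorising leaves about 61% (median split), 50% (80th-percentile cut) or 76% (quintiles). For a strongly skewed variable there may be no loss, or a gain.

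**What to change.** Replace the sentence on normality testing with wording such as:

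> Continuous and score variables will be analysed on their original scale as differences in means between arms, using linear regression with robust (participant-level) standard errors. No variable will be categorised or transformed on the basis of a normality test. Any categorised or transformed version will be pre-specified before data lock and will be supportive only.

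Keep age and other continuous covariates continuous in the adjusted models.

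The cost is one sentence, with no extra data, staff or participants. The small downside is that a mean difference is slightly less intuitive than a percentage; a supportive categorised table can still be shown beside it.
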